## Abstract

**Background:**

Approximately 80% of people with a substance use disorder (SUD) are smokers. Starting SUD treatment offers the opportunity to also quit smoking. The ACT-ATAC project aims to identify the predictors associated with smoking cessation among persons treated for alcohol and/or cannabis use disorder in Barcelona. This manuscript reports its methodology and the experience of carrying it out during the COVID-19 pandemic.

**Methods:**

Mixed methods project with three substudies. Substudy 1 (S1) comprises heterogeneous discussion groups among clinicians. S2 has two prospective cohorts composed of smokers under treatment for alcohol and/or cannabis use disorder and the clinicians in charge of these patients. Participating smokers will be followed for 12 months and interviewed about their substance use and the tobacco cessation services received using the Spanish version of the users’ Knowledge, Attitudes, and Services (S-KAS) scale. The clinicians will be asked about their self-reported practices in smoking cessation using the Knowledge, Attitudes, and Practices (S-KAP) scale. S3 comprises heterogeneous discussion groups with smokers. Data will be triangulated using qualitative and quantitative analyses. To facilitate the recruitment process, the researchers have introduced several strategies (design clear protocols, set monthly online meetings, extend the project, provide gift cards, etc.).

**Discussion:**

The results of S1 were used to develop the questionnaires. S2 required some adjustments due to the COVID-19 pandemic, particularly the follow-up interviews being conducted by phone instead of face-to-face, and the recruitment rhythm was lower than expected. Recruitment will last until reaching at least 200–250 users. The fieldwork could not have been possible without the collaboration of the ACT-ATAC team and the introduction of several strategies.

***Trial registration*** The ACT-ATAC project has been successfully registered at Clinicaltrials.gov [NCT04841655].

## Background

Tobacco use is the single most preventable morbidity and mortality [1]. Though progress has been made in reducing the prevalence of tobacco consumption in the general population [2], high prevalence (75.2% to 85.1%) remains in some vulnerable populations, particularly among people with substance use disorders (SUDs) [3]. Tobacco is responsible for 53% of the deaths in this group, reducing their life expectancy up to 25 years compared to the general population [4].

Smokers with SUDs take up smoking at an early age, consume more cigarettes per day (CPD), and frequently use different tobacco products [3], resulting in increased nicotine dependence [5] and a two to five times lower likelihood of cessation [6]. In SUD treatment settings, tobacco use has been historically considered a minor problem compared to other substances. Smoking was even once considered therapeutic in preventing substance use relapse [7]. People in treatment for SUDs have shown interest in quitting smoking [8] and make more serious attempts (abstinence  ≥ 24 h) when they are offered both psychological and pharmacological assistance [9].

Approximately 81,000 people annually are admitted to specialized treatment centers in Spain for outpatient treatment for SUDs [10]. Alcohol is responsible for four out of 10 admissions, and cannabis for two out of 10. Data from the Spanish Drug Observatory indicate that 44.7% of people admitted to outpatient treatment for alcohol and 83.3% admitted for cannabis use disorder have used tobacco in the previous 30 days [11]. However, only 44% of the SUD Programs in Catalonia (Spain) provide tobacco cessation treatment as part of their portfolios [12].

Given the high concomitant use of tobacco in patients in SUD treatment, its consequences to physical and mental health, and the low deployment of interventions in Spain, there is an urgent need to study which factors promote the introduction of smoking cessation in these programs.

Therapeutic strategies for smoking cessation come from recent studies conducted mainly in the United States and Australia. These studies suggest a variety of therapeutic targets, including the promotion of smoking reduction as an initial goal [13, 14], the combination of cognitive-behavioral interventions and existing pharmacotherapy [15], relapse prevention [16]), extended follow-ups [6], and a comprehensive model in SUD treatment settings and the community that responds to the concomitant use of tobacco and other substances [13].

The optimal time to promote smoking cessation in people with SUDs is controversial [17, 18], mainly due to patients' low motivation to quit and their concerns about how quitting smoking will affect their treatment for quitting the main drug(s) [19]. Thus, some clinicians are reluctant to provide interventions that address tobacco use during SUD treatment [20]. Recent experiences, however, suggest that concurrent interventions are well accepted by smokers being treated for both alcohol [21] and cannabis use [22, 23], reporting satisfactory 7-day smoking abstinence rates similar to the general population (28%) [24] and a lower relapse rate than among those who continue smoking [25].

Simultaneously quitting both substances has both psychological and neurobiological benefits [14]. This approach may also be beneficial from an economic point of view as both treatments can be targeted during a single treatment episode, reducing costs. Yet, simultaneous interventions are less frequent than consecutive interventions. A previous study conducted in Barcelona (Spain) found that smokers with alcohol use disorder who were offered smoking cessation achieved better quit rates for both alcohol and tobacco when both drugs were treated simultaneously [26].

Exploration of the barriers and facilitators to abstinence and understanding what elements affect the psychiatric symptomatology and the main drug use are relevant to patients in SUD treatment. Acquiring such information will allow the scientific community to design personalized approaches to promote cessation [27, 28] within this vulnerable group. Previous studies associated smoking cessation in this population with sociodemographic variables (i.e., low education level, low socioeconomic status) [29] and other components, such as motivation to quit smoking, self-efficacy, previous experience with quitting smoking [30], expected withdrawal symptoms [31], and assessment of the services received [9]. Proactively identifying positive predictors of change among smokers in this population may help promote smoking cessation; the most frequently reported predictors are a high level of motivation, having had previous quit attempts, and reducing the number of CPD [13, 14].

Barriers to addressing tobacco use during addiction treatment have also been identified among clinicians. The main barriers are lack of knowledge and training, the preconception that quitting smoking simultaneously while being treated for use of other drugs may compromise abstinence, and clinicians’ smoking status [20].

The high number of SUD treatment admissions for alcohol and/or cannabis use, the high prevalence of tobacco use, and the limited number of interventions aimed at promoting smoking cessation in this group prompts research to facilitate new and better interventions in these settings. We designed the ACT-ATAC (“*Abandono del Consumo de Tabaco durante la Atención y el Tratamiento para Alcohol y/o Cánnabis*” [Tobacco cessation among smokers under alcohol and/or cannabis treatment]) study, which aims to:

(1) Explore clinicians' perceptions of the barriers and facilitators (individual and contextual) that influence the implementation of smoking cessation interventions, and the appropriateness of simultaneous or sequential interventions aimed at this group.

(2) Describe changes in tobacco use, motivation to quit, and the barriers/facilitators to quit at the start of treatment and after 12 months of follow-up.

(3) Identify the individual and contextual predictors associated with successful smoking cessation among persons treated for alcohol and/or cannabis use disorder in SUD programs in Barcelona.

(4) Identify and compare the level of implementation of smoking cessation services reported by patients and clinicians.

The purpose of this manuscript is to report the methodology employed in the ongoing ACT-ATAC project and the experience of carrying out and adjusting this study during the social restrictions put in place due to the COVID-19 pandemic.

## Methods

### Design

We designed a mixed method observational study (Fig. 1). The ACT-ATAC project began in January 2019 and was conceived as a 36-month study. However, due to the COVID-19 pandemic, we have extended the study for eight more months. At the present time, December 2021, we are in month 35 (Fig. 1) and we foresee the study lasting until the end of June 2023.

**Fig. 1 Fig1:**
[figure not shown]
The ACT-ATAC project flowchart

Mixed method studies include both a qualitative and a quantitative research perspective in which one of the study designs may have a lead role and the other has a more supporting role [32]. In this project, the cohort study is the primary design. The study is divided into the following substudies (S1-S3).

S1 (months 1–11): Phenomenological study with discussion groups directed towards health professionals (corresponding to January 2019–November 2019; carried out before the outbreak of COVID-19 in Spain).

This qualitative phenomenological study with discussion groups used a semi-structured script to answer aim 1. Our target was all healthcare professionals working at one of the 42 SUD programs in the province of Barcelona. Twelve centers were chosen from those that expressed interest according to a geographical distribution criterion to ensure variability of areas, as 65% of the centers in the province belong to the city of Barcelona and the rest to other nearby cities. Clinicians from these SUD centers were recruited via a letter signed by the Head of the Catalan Drug Plan and addressed to program directors, asking them to engage their staff in participating.

### Participants

Participants included all healthcare professionals from the selected SUD programs who work in the mental health field with at least 1 year of experience in the field and agreed to participate and provide informed consent. Clinicians were grouped into three heterogeneous discussion groups (8 to 10 participants each) led by two experts in qualitative research who followed a script of themes to be explored. Themes included (1) barriers and opportunities to address tobacco use among persons in treatment for alcohol and/or cannabis use; (2) health professionals’ opinions on the type of smoking cessation interventions that could be offered to these patients and whether these interventions should be simultaneous or consecutive with the treatment of the main drug, and (3) experiences in helping smokers quit.

### Procedures and statistical analysis

Sessions were recorded and transcribed, preserving participant anonymity and confidentiality, to conduct a thematic categorical content analysis (AC-CT). Thematic axes were proposed to finish constructing the questionnaire needed in the second phase of the study.

S2 (months 11–40): Longitudinal prospective study with smokers in treatment for alcohol and/or cannabis and the clinicians involved (corresponding to November 2019–December 2022; study piloted before the outbreak of COVID-19 in Spain but carried out during and after the severe lockdown of March 2020-June 2020, and currently ongoing).

The second substudy covers aims 2 and 3 and consists of two prospective cohorts composed of (1) smokers in treatment for alcohol and/or cannabis who visited one of the participating SUD programs, who agreed to participate in this study, and had at least one responsible healthcare professional to recruit participants during the first and second year of the study, and (2) the clinicians in charge of these patients.

### Cohort of smokers

#### Participants

Inclusion criteria are (1) being a tobacco user (at least one cigarette per week), (2) initiating treatment for alcohol and/or cannabis in one of the SUD participating program, (3) age  ≥ 18 years, (4) under follow-up by participating clinicians, and (5) providing consent. Exclusion criteria are (1) inability to guarantee a 12-month follow-up (due to anticipated mobility problems, etc.) and (2) severe cognitive impairment and/or other communication problems (i.e., not speaking Spanish or Catalan).

#### Sampling method

The incidence of unassisted smoking cessation is seven ex-smokers per 100 patient-years [33]. We estimate that, among this sample, being in contact with the health system may increase this rate to 10 ex-smokers per 100 patient-years (i.e., a relative risk [RR] of quitting smoking of 2.0). Therefore, to detect this RR assuming an alpha error of 5%, a beta error  < 20%, and losses of 20%, we require 366 participants. The sample size was calculated using the GRANMO program [34]. This sample size is achievable in one year as the 48 centers in the province of Barcelona treat approximately 5000 new cases for alcohol and 1500 new cases for cannabis yearly (target population: 6,500 participants) [12]. On average, the 10–12 selected study centers should treat approximately 1,625 people/year. Smokers in treatment for alcohol and/or cannabis use are being recruited consecutively for one year.

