## Statistical analysis

After finishing the recruitment and follow-up, abstinence and quit attempt incidence rates will be calculated at baseline and at 3, 6, and 12 months according to whether participants have received any type of smoking cessation intervention. We will also calculate the corresponding risk ratios with 95% confidence intervals (CIs) for quitting and quit attempts.

We will assess the association between receiving smoking cessation support and the two primary outcomes (abstinence and quit attempts) using a Poisson regression model with robust variance for several independent variables (the substance of treatment, sex, types of cessation support [e.g., tobacco-related counselling and medication, etc.]), resulting in RRs with their 95% CIs as their estimators. For analysis, we will use SPSS for Windows version 21 with significance set at p  < 0.05.

We will also conduct exploratory factor analysis for testing the psychometric properties of the S-KAS and S-KAP scales.

S3 (months 40–44): Phenomenological study with discussion groups directed towards patients (will be conducted between December 2022 and June 2023).

This qualitative phenomenological study with discussion groups will use a semi-structured script to answer aim 4.

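### The reference quit rate of 7 per 100 patient-years is not reconciled with the protocol's own statement that smokers with SUDs quit less often, so the stated power for RR 2.0 is not supported for this population

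*Protocol article*

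**What the plan says.** The Sampling method section (Cohort of smokers) opens with the reference rate: "The incidence of unassisted smoking cessation is seven ex-smokers per 100 patient-years [33". It does not say which population that rate describes. It then moves to the study's own sample and says that "being in contact with the health system may increase this rate to 10 ex-smokers per 100 patient-years", glossed as "i.e., a relative risk [RR] of quitting smoking of 2.0". The result follows: "assuming an alpha error of 5%, a beta error < 20%, and losses of 20%, we require 366 participants".

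The Background makes two statements that bear on this rate. Smokers with SUDs have "a two to five times lower likelihood of cessation [6"; no comparator or time frame is given. Later, for concurrent interventions in smokers treated for alcohol or cannabis use, it describes studies "reporting satisfactory 7-day smoking abstinence rates similar to the general population (28%) [24".

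The Statistical analysis section sets the comparison: abstinence and quit attempts "according to whether participants have received any type of smoking cessation intervention". The reference group is therefore made up of participants without cessation support. The section on fieldwork during the pandemic lowers the recruitment target to at least 200 to 250.

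**The concern.** For a binary outcome, the reference rate fixes the expected number of events and hence the precision of the relative risk. Every participant is a smoker starting treatment for alcohol and/or cannabis use. The protocol gives a reason to expect fewer quitters in such people, then sizes the study on a rate with no reduction for it. The only adjustment, for contact with the health system, goes the other way.

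If the true unsupported rate is below 7 per 100, the comparison of supported with unsupported smokers rests on very few quitters, and a null result for cessation support would say little. The power claim still matters, because the Discussion justifies extending the study by the need for enough statistical power.

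**Working it through.** **Inputs from the protocol.** Reference rate 7 per 100 patient-years; RR 2.0; alpha 5%; power 80%; losses 20%; 12 months of follow-up; required size 366; current target 200 to 250; factor for SUD smokers two to five; 28% abstinence with concurrent interventions.

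**Assumptions of this check.** Two-sided test, 1:1 split between supported and unsupported smokers, and 12-month risk taken as the annual rate. For the lower rates only, the two- to five-fold factor is taken to divide the 7.

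**Formulas** (arcsine, two independent proportions):
- h = 2·asin(√p2) − 2·asin(√p1)
- n per group = 2(1.960 + 0.842)² / h²
- power = Φ(h·√(n/2) − 1.960)

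**1. Reproducing 366.** For 7% vs 14%, h = 0.2315. This gives n = 293.0 per group, and 293.0/0.8 = 366.2. So 366 does follow from 7% and RR 2.0, but as a number per group. As a total, the same inputs need 2 × 366.2 = 732.

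**2. Candidate reference rates.** 7/2 = 3.5 and 7/5 = 1.4 per 100. On the favourable side, half of 28% is 14%, so that RR 2.0 leads to the 28% of the Background.

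**3. Numbers analysed per group after 20% losses.**
- 366 per group: 366 × 0.8 = 292.8
- 366 in total: 366 × 0.8 / 2 = 146.4
- 250 in total: 250 × 0.8 / 2 = 100
- 200 in total: 200 × 0.8 / 2 = 80

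**4. Power for RR 2.0.**

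| Reference vs supported | h | 366 per group | 366 in total | 250 in total | 200 in total |
|---|---|---|---|---|---|
| 1.4% vs 2.8% | 0.0990 | 22% | 13% | 10% | 9% |
| 3.5% vs 7% | 0.1591 | 49% | 28% | 20% | 17% |
| 7% vs 14% | 0.2315 | 80% | 51% | 37% | 31% |
| 14% vs 28% | 0.3482 | 99% | 85% | 69% | 60% |

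Example, 3.5% vs 7% with 366 per group: 0.1591 × √(292.8/2) = 1.926; 1.926 − 1.960 = −0.034; Φ(−0.034) = 0.49. The pooled normal formula agrees with every cell to within about one percentage point.

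**5. Expected quitters in the unsupported group, with 366 in total.** 146.4 × 0.035 = 5.1 and 146.4 × 0.014 = 2.0, against 146.4 × 0.07 = 10.2 at the stated rate.

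**The case against.** A reader might infer that the protocol itself puts the quit rate at 1.4 to 3.5 per 100 and that the power is thereby shown to be wrong. The documents do not support that. They do not name the population behind the 7, nor the comparator, time frame or measure behind the two- to five-fold factor. Dividing one by the other is valid only if the factor is an annual relative rate against the population that supplied the 7. The loss of power in the two lower rows is conditional.

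Two further points favour the authors. The primary outcome is 7-day abstinence, which is more lenient than an incidence of ex-smokers, and eligibility begins at one cigarette per week, so events may be more frequent than the 7 suggests. The Background also reports 28% abstinence, similar to the general population, in smokers treated for alcohol and cannabis use. That figure comes from smokers who were given an intervention, so it is not a rate for the unsupported group, but it does weigh against assuming a uniform reduction.

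A second tempting inference is that power above 80% would hold if only 7 per 100 were right. It would not if 366 is the total: power at 7% vs 14% is then about 51%. The stated rise from 7 to 10 is also a relative risk of 10/7 = 1.43, not 2.0. These are separate faults, and the reference rate is not the main cause.

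Nor does it follow that every predictor analysis would be uninformative. Precision for sex or substance of treatment depends on quitters across the whole cohort.

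What remains is that the sample size paragraph neither applies the Background statement nor explains why it does not apply. That holds even if 366 is read per group and RR 2.0 is accepted.

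**Conclusion.** The concern holds as a failure to reconcile the sample size with the Background. The claim of at least 80% power for RR 2.0 rests on a reference rate of unstated origin, and the protocol's own text gives grounds to expect both lower and higher values. Over 1.4% to 14%, power with 366 in total runs from about 13% to 85%; with the 200 to 250 now planned it runs from about 9% to 69%. At the planned enrolment, no rate in that range reaches 80%.

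These figures rest on a two-sided 5% test, an even split, 20% losses and RR 2.0. The lower end also rests on applying the two- to five-fold factor to the 7, and the upper end on halving the 28%. The reference rate is one of several reasons why the stated power fails.

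**What to change.** In Sampling method, state which population the 7 per 100 describes, and either justify it for smokers in SUD treatment or replace it. Reconcile it explicitly with the two Background statements and with the 7-day abstinence outcome. Withdraw the claim of more than 80% power for RR 2.0. Report instead the power, or the expected width of the confidence interval for the RR, over a range of reference rates (for example 1.4% to 14%) at the number actually to be enrolled.

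The cost is one rewritten paragraph and one recalculation. No extra enrolment and no change to study procedures are needed. The stated power will look less favourable.

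### The sample size is built on health-system contact versus unassisted quitting, while the analysis compares supported with unsupported patients inside the cohort, so the stated power is not shown for the planned contrast

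*Protocol article*

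**What the plan says.** **Sampling method (cohort of smokers).** The reference is an outside figure: "The incidence of unassisted smoking cessation is seven ex-smokers per 100 patient-years". For the study sample, "being in contact with the health system may increase this rate to 10 ex-smokers per 100 patient-years". The text describes this as "a relative risk [RR] of quitting smoking of 2.0". With a 5% alpha error, a beta error below 20% and "losses of 20%, we require 366 participants".

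**Participants (cohort of smokers).** Every participant must be "initiating treatment for alcohol and/or cannabis in one of the SUD participating program" and must be followed by a participating clinician.

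**Statistical analysis.** Abstinence and quit-attempt rates are calculated "according to whether participants have received any type of smoking cessation intervention". A Poisson model with robust variance then estimates RRs for receiving cessation support. No comparison with the outside rate of 7 per 100 is described.

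**Fieldwork and strategies.** The recruitment goal is now at least 200 to 250 participants. The Discussion says the study was extended so that there would be enough statistical power for the analysis.

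**The concern.** Taken literally, the exposure behind the planning RR is contact with the health system. Nobody in the cohort lacks that contact, so the cohort has no internal reference group for it. The analysis uses a different exposure, receipt of cessation support, and both of its groups are in contact. On the paragraph's own reasoning, unsupported patients would also gain from contact, so their rate need not be 7 per 100.

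Two inputs that the planned comparison needs are absent: the quit rate expected among unsupported patients already in care, and the share expected to receive support. This is more than detail left to a fuller document, because the article states both a power basis and an analysis, and the two do not visibly describe the same groups.

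At stake is how a null result would be read. A reader who believes the study had more than 80% power could take a non-significant association between support and abstinence as evidence that support does not help.

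**Working it through.** **Inputs from the Protocol article.** Rates of 7 and 10 per 100 patient-years, RR 2.0, alpha 5%, power 80%, losses 20%, N = 366 (Sampling method); current target 200 to 250 (Fieldwork and strategies).

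**Assumptions.** Two-sided test; 12-month risk equal to the rate per 100 patient-years; share supported 20% to 70%; no covariate adjustment and no clustering by centre.

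**1. Reproducing 366.** Arcsine formula for two independent proportions:

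n per group = 2 × [(1.960 + 0.8416) / (2·asin√p2 − 2·asin√p1)]²

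- 7% vs 14% (RR 2.0): the denominator is 0.7670 − 0.5355 = 0.2315, so n = 293.0 per group. After losses, 293.0 / 0.8 = 366.2. This matches the stated figure, as the size of **one** group. Two groups would need about 732.
- 7% vs 10% (the stated rates; 10/7 = 1.43, not 2.0): 1,346 per group, or 1,683 after losses. This does not match.
- One-sample test of 10% against a fixed 7%: [1.960·√(0.07 × 0.93) + 0.8416·√(0.10 × 0.90)]² / 0.03² = 629, or 787 after losses. This does not match.

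**2. Power for the planned contrast on the most favourable reading.** Take unsupported patients at 7% and supported at 14%. With N analysed and share f supported:

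- n1 = N(1 − f), n2 = N·f, p̄ = 0.07(1 − f) + 0.14f
- SE0 = √[p̄(1 − p̄)(1/n1 + 1/n2)]
- SE1 = √[0.07 × 0.93/n1 + 0.14 × 0.86/n2]
- power = Φ[(0.07 − 1.96·SE0) / SE1]

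Example, N = 366 × 0.8 = 293 and f = 43%: n1 = 167, n2 = 126, p̄ = 0.100, SE0 = 0.0354, SE1 = 0.0367. Power = Φ(0.016) = 51%.

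| Analysed | f = 20% | 30% | 43% | 50% | 70% |
|---|---|---|---|---|---|
| 293 (366 less 20%) | 42% | 48% | 51% | 50% | 38% |
| 250 | 38% | 43% | 45% | 44% | 33% |
| 200 | 33% | 37% | 38% | 36% | 26% |
| 160 (200 less 20%) | 28% | 31% | 31% | 30% | 21% |

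**3. How much of the shortfall is due to the contrast itself?** Restore the group size to 293 per group (586 analysed) and keep RR 2.0:

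- 7% vs 14%, 43% supported: 79%, against 51% with 293 in total.
- 10% vs 20%, equal groups: 93%, against 67% with 293 in total.

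With 293 in total and equal groups, moving the reference from 7% to 10% at a fixed RR of 2.0 raises power from 50% to 67%. So the low figures in step 2 come from using a per-group number as a total and then lowering the target. The contrast problem is of another kind: the inputs for the planned comparison are not given.

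**The case against.** The strongest reply is that the outside reference describes unassisted quitting, and that the analysis splits patients by whether they were assisted. Read that way, the two contrasts nearly coincide. The numbers can even be made to agree: with 7% unsupported, 14% supported and 43% supported, the cohort average is 0.57 × 7 + 0.43 × 14 = 10.0%, which fits 7, 10 and RR 2.0 together. The Background reports that 44% of programmes in Catalonia offer cessation treatment, and 0.56 × 7 + 0.44 × 14 = 10.1%.

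This reading is possible, and it rules out one stronger inference. A reader might conclude that the power belongs to a comparison the study never makes. The text does not support that as fact, because unassisted may have been meant as unsupported. But the paragraph does not say so: it credits the rise to health-system contact, and the 44% is a share of programmes, not of patients. Nor does the reading rescue 366, which under it is a per-group size.

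A second inference, that the choice of contrast causes the loss of power, also fails, as step 3 of the working shows.

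A third reply is that this is an observational cohort already recruiting, and its RRs and confidence intervals will be computed the same way whatever the paragraph says. That is true and limits the consequence. The article still states alpha, beta and RR, sets a significance level, and gives statistical power as a reason for the extension.

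**Conclusion.** The concern holds in a limited form. The sample-size paragraph does not identify the groups that the analysis compares. It gives neither an unsupported quit rate for patients in care nor an expected supported share, so power above 80% is not shown for supported versus unsupported patients.

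On the reading kindest to the plan, power for RR 2.0 is about 38-51% with 293 analysed, 33-45% with 250 and 26-38% with 200. These figures rest on the assumptions listed in the working, above all the 20% to 70% supported share, which the article does not give. They measure the combined effect of the group size and the reduced target. They should not be cited as the cost of the contrast mismatch. The gap between 10/7 = 1.43 and the stated RR of 2.0 is a related but separate error, and correcting it alone would leave the contrast undefined.

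**What to change.** Rewrite the sample-size paragraph in Sampling method so that:

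- the planned contrast is patients who did versus did not receive cessation support, within the cohort;
- the assumed quit rate for unsupported patients already in care is stated, with its basis;
- the assumed share receiving support is stated, with a range;
- power, or the detectable RR, is given for that contrast at the 200 to 250 now to be enrolled, after the 20% losses, with the number per group shown;
- the health-system-contact effect no longer serves as the basis, since the cohort has no out-of-contact group from which to estimate it.

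The cost is one paragraph and one recalculation. Recruitment, data collection and the Poisson analysis stay as they are, and no extra enrolment is needed. The stated power will be less favourable, and the Discussion's remark about having enough statistical power should be brought into line with it.
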